## Background

### Clinical and prognostic assessment of chronic obstructive pulmonary disease

Chronic Obstructive Pulmonary Disease (COPD) is a major public health problem, as there is considerable underdiagnosis and a high morbimortality. It is the fourth cause of death among males in European countries and its prevalence is expected to continue to increase [1]. Available epidemiological data show a wide variability in the incidence, prevalence and mortality in different countries [2]. In Spain, the EPI-SCAN study [3] found an overall prevalence for COPD of 10.2 % (CI 95 %: 9.2–11.1 %), higher among men than women (15.1 %/5.6 %), with 4.4 % (CI 95 %: 3.8–5.1 %) of cases classified as moderate to very severe (Stages II-IV of the Global Initiative for Chronic Obstructive Lung Disease [GOLD] classification).

COPD is characterized by a chronic poorly reversible airflow limitation, which is usually progressive if appropriate measures are not taken. Although the value for maximum forced expiratory volume in the first second (FEV1) has been the most commonly used prognostic variable, there is increasingly more evidence that FEV1 does not express the complexity and heterogeneity of COPD. Exercise tolerance, exacerbations, comorbidity, social support and quality of life are all dimensions that have been shown to be important predictors of mortality, each with its own strengths and limitations [4]. This has not led to abandoning the use of FEV1, with different cut-off thresholds to the classic ones, as a simple element with a high predictive value [5].

In its 2011 revised version, the GOLD [6] proposed a combined assessment of COPD based on the patient’s level of symptoms (measured on the modified Medical Research Council [MRC] dyspnoea scale or the COPD Assessment Test [CAT] questionnaire) and on the frequency of exacerbations in the last year or the degree of intensity of the obstruction (FEV1). This assessment has established the basis for drawing up guidelines for the individualized therapeutic management of COPD patients. Even though an advance, it caused controversy: depending on the criteria used for the classification, the allocation of patients could vary [7]; and the prognostic capacity of each group has also varied in different studies [8, 9].

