For use in Primary Care (PC), the requirements for an index are [13]: a) it is simple to record and calculate; b) its components should be easy to record and register; c) its components should individually be clinically significant; d) it should be able to predict severity, with quality of life and mortality as outcomes; and e) it should predict future exacerbations and consumption of resources. With these criteria, the following indices could be selected for use in PC:The ADO (Age, Dyspnoea, Obstruction) index, derived from the BODE index in which age is included and with a higher predictive value than the original BODE; i.e., able to predict the probability of a specific patient dying in the next 3 years [14]. Recently, this scale has been recalibrated [15] in a very large cohort.The BODEx index, a simplified version of BODE in which the 6MWT is eliminated, substituting it with exacerbations without losing predictive capacity [16]. In the updated *GesEPOC* of 2014 [17], its use is proposed as a guide for referring patients and for selecting pharmacological treatment. This index is well known in Spain, but to date has had only limited use in the rest of Europe.The DOSE (Dyspnoea, Obstruction, Smoking, Exacerbation) index is the only one initially designed in PC, and although it first focused on health outcomes, its prognostic capacity has been demonstrated for mortality [18, 19].

The ADO and BODEx indices were designed for large cohorts in a hospital setting, in some cases with outpatients. To be applied in a different care setting, their validation is recommended, as has already been partially done in some studies [20, 21]. For the designers of each index, each one is applicable in primary care and each one has the best prognostic capacity. Comparing published studies, the BODEx [16] has an area under the curve (AUC) of 0.75, which has been exceeded by the modified ADO index [15] with an AUC of 0.80, while the value for the AUC for DOSE was not published [18].

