To sum up, the ADO and BODEx indices validated predominantly in cohorts from hospital settings can have a different prognostic capacity in a PC setting, due to the differences in severity and other clinical and social characteristics that depend on the setting in which patients are treated. Therefore, we need to verify if the capacity of these indices to discriminate and calibrate patients is maintained when they are applied in primary care.

Besides, the ADO, BODEx and DOSE indices, obtained in the PC setting, can show a different prognostic capacity in each subgroup, according to the GOLD classification and for each phenotype according to the *GesEPOC* classification. We expect that the prognostic capacity is better in groups C and D of the GOLD classification and in the exacerbator phenotypes of the *GesEPOC*, because these patients may be more widely represented in the population treated in the hospital and have lower intragroup variability. The prognostic capacity for the GOLD subgroups will vary according to whether CAT or MRC is used for their classification.

The aim of our study is to assess the prognostic capacity of the ADO, BODEx and DOSE indices in primary care, and to validate the models obtained in subgroups of patients, classified by the new combined assessment proposed in the revised GOLD methodology of 2011 and according to the phenotypes proposed in the updated *GesEPOC* of 2014. Besides, we want to confirm that the prognostic capacity of all indices increases if the number of exacerbations is substituted by the interval between them and to assess the impact on health of the patient’s lifestyle, social network and adherence to treatment.

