### Data analysis

The analyst will identify incomplete data and communicate it to the relevant professional for the particular patient. Appropriate test and statistical treatment (multiple imputations) of lost values will be performed.

To assess the discriminatory capacity of the different indices studied (ADO, BODEx and DOSE), logistic regression models and Cox proportional hazard models will be constructed. Initially, the possible non-linear effect of the indices will be studied by using Structured Additive Regression (STAR) models with penalised splines. Subsequently, we will assess different aspects of the regression models: discrimination, calibration and diagnostic precision. For calibration, the Brier score will be used, together with the Hosmer–Lemeshow test for goodness of fit and graphs of the non-parametric estimates of the association between the expected frequencies and those found for the model. To determine the discrimination of the models, ROC curves (and the corresponding AUC) will be calculated. For survival models, the time-dependent ROC will be estimated, as well as its graphical representation. Diagnostic precision will be calculated as the proportion of patients classified incorrectly. For this purpose, the classification rule shall be as follows: each patient will be classified as belonging to the group for which the predicted probability is higher. To correct against optimism, bootstrap techniques will be used.

Statistical analyses will be carried out using BayesX software for the Structured Additive Regression (STAR) models, freely accessible at http://www.statistik.lmu.de/~bayesx/bayesx.html the package*s rms, survival, surv2sampleComp, pROC, risksetROC* of software R [28, 29], available free at http://cran.r-project.org.

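### GOLD groups are cut on components of the indices, so a difference in subgroup AUC (between groups, or CAT versus MRC) does not by itself show that an index works differently

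*Protocol article*

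**What the plan says.** The Background (Clinical and prognostic assessment) describes the GOLD 2011 grouping. One axis is symptoms, "measured on the modified Medical Research Council [MRC] dyspnoea scale or the COPD Assessment Test [CAT] questionnaire". The other rests "on the frequency of exacerbations in the last year or the degree of intensity of the obstruction (FEV1"). The same section lists the indices. One is "The ADO (Age, Dyspnoea, Obstruction) index, derived from the BODE index in which age is included". BODEx contains body mass index, obstruction, dyspnoea and exacerbations. DOSE contains dyspnoea, obstruction, smoking and exacerbations. The Predictors section names the MRC scale as the dyspnoea measure for ADO and BODEx, and says the GOLD assessment will be calculated in four versions.

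Two expectations follow in the Background. The first is "We expect that the prognostic capacity is better in groups C and D of the GOLD classification", and likewise in the exacerbator phenotypes, "because these patients may be more widely represented in the population treated in the hospital and have lower intragroup variability". The second is: "The prognostic capacity for the GOLD subgroups will vary according to whether CAT or MRC is used for their classification".

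Under Data analysis: "To determine the discrimination of the models, ROC curves (and the corresponding AUC) will be calculated". Calibration (Brier score, Hosmer-Lemeshow, calibration graphs) and the misclassification rate are planned as well. The article does not mention that the groups and the indices share components.

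**The concern.** An AUC depends on two things: how strongly the index relates to death, and how widely the index is spread among the patients assessed. Splitting a cohort on components of the index narrows the spread inside each group, and not equally. MRC grouping cuts directly on an index component. CAT is in none of the indices, so CAT grouping cuts only on a correlate of dyspnoea. ADO keeps age, which GOLD does not use. Subgroup AUCs can therefore differ between groups, between GOLD versions and between indices when each index has exactly the same relation to mortality in every patient.

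The reason given for the first expectation also points the wrong way if it refers to the index. Other things equal, less spread lowers the AUC.

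Validation in GOLD subgroups is part of the stated aim, and the Discussion expects the subgroup assessment to influence referral and individualised treatment. A truncation effect read as a property of the index would mislead there.

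**Working it through.** **1. The plan's own figure.** Inputs from Sample size: AUC 0.75, alpha 0.05, power 0.90, kappa 8 (controls per case). I used the Obuchowski one-curve formula, taken to be what the quoted function computes, with a two-sided alpha:
- A = 1.414 × z(0.75) = 0.954
- V0 = 0.0099 × (8 + 8/8) = 0.0891
- Va = 0.0099 × exp(-A²/2) × [(5A² + 8) + (A² + 8)/8] = 0.0858
- cases = (1.960√V0 + 1.282√Va)² / 0.25² = 14.8; controls = 8 × 14.76 = 118.1; total 132.8
- 132.8 × 3 groups × 1.20 = 478

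The article gives 15 deaths and 118 survivors (133) per group and 477 in all, so its figures reproduce.

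**2. Why spread drives the AUC.** With one logistic slope and a roughly normal index, AUC ≈ Φ(z(0.75) × r) = Φ(0.674 r). Here r is the SD of the index in the group relative to the whole cohort, and the cohort AUC is 0.75.

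**3. Simulation with no subgroup effect.** One risk function applies to all patients, with mortality 12.5 % and overall AUC 0.75. Groups are formed by MRC or by a correlated CAT (correlation 0.6), and by poor FEV1 or frequent exacerbations, either one sufficing for high risk. Cut-offs, index weights and correlations are assumptions, because the article does not print them. One setting (BODEx-like index, skewed components, component correlation 0.2):

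| Group | r (MRC) | Φ(0.674 r) | AUC, MRC | AUC, CAT |
|---|---|---|---|---|
| A | 0.48 | 0.627 | 0.624 | 0.652 |
| B | 0.53 | 0.640 | 0.640 | 0.675 |
| C | 0.58 | 0.652 | 0.652 | 0.676 |
| D | 0.69 | 0.679 | 0.675 | 0.701 |

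The formula in step 2 accounts for the pattern. In the same setting an ADO-like index, also 0.75 overall, had AUC 0.698 in MRC group A, against 0.624 for BODEx.

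**4. Range over six settings** (component correlation 0 to 0.4, two exacerbation rates, skewed or symmetric components):
- Within-group AUC was 0.62 to 0.75; a further set of settings reached down to 0.60.
- CAT grouping exceeded MRC grouping in every group and setting, by about 0.01 to 0.036 (up to 0.07 in another set).
- D exceeded A and B throughout; D minus A was 0.004 to 0.056 (up to 0.069 in another set).
- Mean of C and D minus mean of A and B was +0.004 to +0.033 (up to +0.049 in another set).
- C alone was not reliable. It was 0.673 against 0.685 in B in one setting (BODEx, fewer exacerbations, CAT), and 0.658 against 0.667 in A in another (symmetric, correlation 0.3, MRC).
- C and D usually, but not always, had the wider spread. In that symmetric setting r was 0.66 in A and 0.65 in D.

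**5. A single risk criterion.** The four GOLD versions could mean MRC or CAT crossed with FEV1 or exacerbations, one risk criterion each. Then mean of C and D minus mean of A and B was -0.014 to +0.007 in one set of simulations and -0.020 to +0.027 in another. The sign is not fixed.

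**6. Against sampling error.** Hanley-McNeil with AUC 0.75, 15 deaths and 118 survivors: Q1 = 0.75/1.25 = 0.600 and Q2 = 2 × 0.5625/1.75 = 0.643. Variance = [0.1875 + 14 × 0.0375 + 117 × 0.0804]/1770 = 0.00571, so SE = 0.076. For a difference between two independent groups, SE = 0.076 × √2 = 0.107. An artefact of 0.004 to 0.056 would then produce the expected order of two groups with probability Φ(0.004/0.107) = 0.51 to Φ(0.056/0.107) = 0.70. The CAT and MRC versions regroup the same patients, so that contrast has a smaller error than 0.107; I have not calculated it.

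**The case against.** A reader might infer that C and D must look better by construction and that the study is bound to confirm its hypotheses. The documents do not support that. The article gives no cut-offs and no rule for when exacerbations and FEV1 disagree. Under a single risk criterion the advantage of C and D can vanish or reverse, C alone is unreliable even when either criterion suffices, and chance variation with 15 deaths per group exceeds the artefact.

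A reader might also infer that the study will decide by contrasting raw AUCs. Data analysis describes no between-group AUC test, such detail commonly sits in an analysis plan that is not shown, and calibration is planned too.

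Nor is a low AUC within group A an error. It truly describes how well the index separates those patients, and if age keeps ADO discriminating there, that is a real advantage in use.

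Finally, "have lower intragroup variability" may mean clinical homogeneity rather than spread of the index, and it is only one of two reasons given.

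All of this stands. What remains is that the article frames differences between subgroups and between CAT and MRC as findings about prognostic capacity, while the grouping variables overlap with the index components. Calibration results do not correct the reading of an AUC difference. Low precision does not remove a shift that more data would leave in place.

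**Conclusion.** The concern holds as a caution about interpretation, with a cheap remedy. The overlap of components is plain in the document. With no true difference between patients, subgroup AUCs fall to about 0.60 to 0.75 from 0.75 overall. The firmest result is that CAT grouping gives higher within-group AUCs than MRC grouping (roughly 0.01 to 0.07), in every setting tried. Higher AUCs in D, and in C and D combined, appear when either criterion makes a patient high risk; this is small and not assured under a single criterion. All magnitudes rest on assumed distributions, cut-offs, weights and a CAT-dyspnoea correlation of 0.6. The study would not automatically confirm its expectations. But an observed subgroup or CAT/MRC difference in AUC would not, alone, show that an index works differently, and the lower-variability reason needs rewording.

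**What to change.** - For each GOLD group and each GOLD version, report beside the observed AUC the AUC expected from that group's own index distribution under one common model.
- Claim different index performance only where observed departs from expected, supported by the index-by-group slope difference and by within-group calibration (observed over expected deaths).
- Keep the raw AUCs as descriptions of discrimination within each group.
- Reword the Background reason: say what variability is meant, and that less spread of the index lowers the AUC, other things equal.
- State for each of the four GOLD versions which criteria define high risk, since the direction of the effect depends on it.

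The cost is some wording and slightly more analysis, with no new patients or data. Subgroup claims become more cautious, and with about 15 deaths per group the slope and calibration estimates will be imprecise as well.

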## Method/design

### Design

Open, prospective and multi-centre validating and updating scales study. Patient recruitment started in February 2015 and will last until Dec 31th, 2016. The patients will be followed for 5 years since their recruitment.

Standards of Reporting adhere to the SPIRIT 2013 Statement for protocols.

### Setting

Primary Care Centres, from Vigo Health Authority (Galicia, Spain) and from Balearic Islands Health Authority (Balearic Islands, Spain). Through these centres, doctors/nurses potentially willing to participate were identified during national and international scientific meetings, both in Spain (Aragón, Canarias, Cataluña) and other European countries (Croatia, Bulgaria, Macedonia, Germany and Romania). Subsequently, General Practitioners (GPs) and/or Nurses were invited and informed by e-mail about the description of the background and objectives of the study, as well as the implications of their participation. There are 36 health centres involved.

Study sites can be found in authors affiliations.

### Subjects

Patients diagnosed with COPD. The eligibility criteria for those studied were similar to those used in the original derivation of the models.

#### Inclusion criteria

patients with a moderate-severe obstruction, defined by a FEV1 lower than 80 % of the expected post-bronchodilator FEV in the presence of a FEV1 quotient/forced vital capacity (FVC) lower than 70 %, diagnosed with COPDpatients in a stable phase of COPD, clinically defined as at least 6 weeks since the last exacerbationacceptance to participate in the study by providing written informed consent.

#### Exclusion criteria

patients diagnosed with cystic fibrosis, or bronchiectasis that is clinically significant or of a different origin to COPD (tuberculosis, childhood infections, immunodeficiencies, and severe cognitive or mobility impairment)patients diagnosed with a severe chronic disease, besides COPD (active malignancy, AIDS, heart failure, severe kidney or liver failure, etc.).

### Patient recruitment

The healthcare professionals identified potentially eligible cases, within their quota of assigned patients, through electronic medical records review (10 per professional). Those patients who are diagnosed with COPD will be included, provided that they fulfil the inclusion criteria as explained previously. After obtaining the informed consent, patients will be incorporated in the study if they have already been correctly diagnosed with COPD. The results of a test taken in the last 6 months during a stable phase will be considered valid; if the last test was more than 6 months ago, a new spirometry test will have to be taken. The study personnel will assess whether the patients have COPD stage II–IV using portable and hand-held spirometry. For our purpose, we will determine postbronchodilator FEV1 and Forced Vital Capacity as a measure for airflow obstruction. Ten minutes before measuring lung function, patients will inhale two puffs of 100 μg salbutamol through a spacer. Once a diagnosis is established, the severity of the obstruction is classified in relation to the post-bronchodilator FEV1 value, expressed as a percentage of the expected level.

The undertaking of the spirometry test and its interpretation will be the responsibility of specially trained staff, who has taken an accredited and tutored theoretical and practical course.

### Outcome variables

Survival (time to event) without exacerbation will be assessed during 5 years since patient recruitment. In addition, mortality (time to event) from all causes and those specifically due to respiratory causes will be analysed as health outcome at the end of the study. Data source will be EMR and death registry data if needed. Blind assessment of the outcome to be predicted is not feasible.

Exacerbations are defined as any sustained increase in respiratory symptoms (dyspnoea, cough and/or expectoration) that require modification of the usual treatment and/or hospital care -visit to the Emergency Room or admission- (for the BODEx index), as well as the exacerbations identified at the PC emergencies department (but without changing subsequent treatment). In this definition, admissions for pneumonia, pulmonary embolism and other causes of complications in COPD are not included.

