### Predictors

Assessment of predictors is done by GPs/nurses at baseline, without knowledge of the participant’s outcome, following the indices (ADO, BODEx, DOSE) definition. Formulas to calculate them are available in Additional file 1: Table S1.

They will be recorded in a specific database along with detailed patient history: date of birth, sex, height, weight, and body mass index. The spirometry test will be carried out according to protocol recommendations and the date of the first spirometric diagnosis of COPD will be recorded. Dyspnoea will be assessed according to the scale proposed by the British Medical Research Council for the ADO and BODEx indices. Associated diseases will be evaluated using the Charlson Comorbidity Index and COMCOLD, and the presence of other relevant illnesses, not included in Charlson, will be recorded, such as myopathy, osteoporosis, obstructive sleep apnoea-hypopnoea syndrome, and anxiety and depression disorders. The COPD Assessment Test (CAT) questionnaire will be used to assess the impact of COPD on the daily life and welfare of the patient, and its results will be used for categorisation according to the revised 2011 GOLD classification. Participating patients will be asked about tobacco consumption (packets/year), alcohol consumption (yes/no, units/week), physical exercise (Physical Activity Questionnaire short form (IPAQ), daily physical activity intense/moderate/low), current respiratory pharmacological treatment (in the stable phase), influenza and pneumococcal vaccine status, having received advice about their lifestyle and evaluation of the social support of the patient. The patient will be classified in accordance with the phenotypes defined by the *GesEPOC* [17].

The number of exacerbations in the previous years will be counted, in accordance with each index definition.

The ADO and modified ADO (from 0 to 14) indices, the BODEx index, DOSE index, Charlson index, COMCOLD index and the combined assessment of the GOLD score using the four possible models will be automatically calculated when introducing the variables that make up the computerised database.

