### Independent variables in the follow-up

The follow-up will be undertaken by clinical visits every 6 months. When the patient cannot make the appointment, follow-up will be by telephone interview or a review of the EMR. Information about the date of clinical exacerbations, admissions, visits to the emergency department (primary care or hospital) and mortality will be obtained by a review of the patient’s medical record, contact with the patient’s family and/or passive follow-up (from hospital and mortality records). Survival will be evaluated after 5 years. If cases are referred to a second care level, any specialist care appointments will be recorded.

Adverse events and dropouts during follow-up will be recorded, with the reason for them.

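### The exacerbation outcome excludes pneumonia, embolism and similar causes only when the patient is admitted, so whether an episode counts depends on care level and not on diagnosis

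*Protocol article*

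**What the plan says.** All from the protocol article.

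- **Outcome variables, inclusion.** "Exacerbations are defined as any sustained increase in respiratory symptoms (dyspnoea, cough and/or expectoration"), with the care threshold "that require modification of the usual treatment and/or hospital care -visit to the Emergency Room or admission- (for the BODEx index"). No cause is required or ruled out.
- **Outcome variables, added events.** The definition also takes in primary care emergency contacts: "as well as the exacerbations identified at the PC emergencies department (but without changing subsequent treatment").
- **Outcome variables, exclusion.** "In this definition, admissions for pneumonia, pulmonary embolism and other causes of complications in COPD are not included".
- **Outcome variables, use.** "Survival (time to event) without exacerbation will be assessed during 5 years since patient recruitment".
- **Background.** A stated aim is to show that every index predicts better when the interval between exacerbations replaces their number.
- **Predictors, baseline count.** "The number of exacerbations in the previous years will be counted, in accordance with each index definition".
- **Independent variables in the follow-up.** "Information about the date of clinical exacerbations, admissions, visits to the emergency department (primary care or hospital) and mortality will be obtained" from records, family contact and passive sources. The cause of an admission or visit is not among the items listed.

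**The concern.** The inclusion rule is broad and indifferent to cause. The only exclusion takes effect at hospital admission. If it is meant to keep worsenings with another explanation out of the exacerbation outcome, it does so only for admitted patients and leaves the same diagnoses in for everyone else. Of two patients with the same diagnosis, the one managed outside a ward has an event and the one who needed a bed does not.

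Two analyses are exposed: time to first exacerbation over 5 years, and the interval between exacerbations. Both would mix the disease process with the decision to admit. That decision follows severity and can differ between health systems, and the Abstract describes 36 centres in 6 high, medium and low income countries.

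**Working it through.** No figure in the protocol bears on this point, so there is nothing to reproduce. The check is of the text, followed by an illustration on assumed values.

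**1. Apply the definition to one diagnosis.** Take a pneumonia with a sustained increase in cough and dyspnoea.

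| How it is managed | Meets the inclusion rule? | Reached by the exclusion? | Counted? |
|---|---|---|---|
| GP changes treatment, no hospital contact | Yes | No | Yes |
| Emergency room, sent home | Yes | No | Yes |
| Admitted | Yes | Yes | No |

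**2. Is the word for admission just loose?** The inclusion sentence lists an emergency room visit and an admission as two different forms of hospital care. Read consistently, the exclusion reaches the second only. No other section extends it to primary care or to emergency care without admission.

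**3. Effect on the two analyses.**
- *Time to first exacerbation.* An uncounted admission matters only if it would have been the first event. The event time then moves to the next qualifying episode, or the patient is censored.
- *Interval between exacerbations.* Take episodes at times t1 < t2 < t3. If the one at t2 is an excluded admission, the two intervals (t2 − t1) and (t3 − t2) become one interval of (t3 − t1). The mean interval goes from (t3 − t1)/2 to (t3 − t1), so it doubles for that patient.

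**4. Scale, on assumptions.** Let s be the share of qualifying episodes due to the named diagnoses (assumed 5-20 %) and h the share of those admitted (assumed 20-80 %).
- Dropped share of all episodes = s × h. Lowest: 0.05 × 0.20 = 0.01. Highest: 0.20 × 0.80 = 0.16.
- Share of counted episodes that are the same diagnoses without admission = s(1 − h)/(1 − s × h). Lowest: 0.05 × 0.20/0.96 = 0.01. Highest: 0.20 × 0.80/0.96 = 0.17.

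The two ends do not occur together: a high h drops more and leaves fewer in, a low h the reverse. The ranges show only that the wording could touch anything from a negligible to a noticeable part of the events.

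**5. What is not touched.** Mortality, all-cause and respiratory, does not use the exacerbation definition, and the sample size rests on expected deaths.

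**The case against.** **The wording may be shorthand.** The authors may have meant to exclude alternative diagnoses at any care level, and the follow-up section speaks of clinical exacerbations, which hints at attribution by the clinician. This is possible. But the text separates emergency visits from admissions one sentence earlier, and nothing states the wider rule, so sites have only the narrower one to apply.

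**The episode is not lost.** This stands. Dates of admissions and emergency visits are collected, a death still counts, and an episode for which the GP changed treatment before admission may already have counted. The gap concerns the exacerbation outcome alone. Later repair is uncertain because the listed items do not include cause.

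**A reader might infer a bias towards no effect**, since age, dyspnoea and obstruction are index items and plausibly raise the chance of admission. The documents do not support this as a general result. Assume a true ratio of 2.0 for all worsenings between high- and low-score patients, and admission of 50 % and 20 %.
- Equal share of these diagnoses, 5 % in both groups: the current rule gives 2.0 × 0.975/0.99 = 1.97, and exclusion by diagnosis gives 2.0. The current rule attenuates.
- Unequal share, 20 % in high-score and 10 % in low-score patients: the current rule gives 2.0 × 0.90/0.98 = 1.84, and exclusion by diagnosis gives 2.0 × 0.80/0.90 = 1.78. The current rule now gives the larger ratio.

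The sign depends on shares that the documents do not give. These are also event-rate ratios, whereas the outcome is time to event and the planned performance measures are AUC, time-dependent ROC, Brier score and calibration.

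**A reader might also infer that the baseline exacerbation count is affected**, because the definition carries a BODEx tag. The Predictors section says that the count follows each index's own definition, with formulas in an additional file that is not shown. That inference is not supported.

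**Some of the remedy is operational detail.** A closed diagnosis list can be left to the full protocol, and its absence from an article is no defect. The care-level exclusion is different: it is a rule that the article states.

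**Conclusion.** The point holds for the follow-up exacerbation outcome. As written, the exclusion works by care level: the named diagnoses count when managed without admission and do not count when admitted. Exacerbation-free survival and the interval between exacerbations thereby depend on severity and on admission practice across centres and countries.

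The conclusion rests on reading the definition as it stands and needs no numerical assumption. The direction and size of any bias in the indices' performance cannot be derived from the documents; the percentages under the check are illustrations on assumed inputs. The main aim, validating the indices for mortality, is unaffected. This is worth correcting because exacerbations are a named outcome, the interval hypothesis is a stated aim, and the correction is cheap.

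**What to change.** For the follow-up outcome, state the exclusion by diagnosis at every care level. Suggested wording: episodes attributed to pneumonia, pulmonary embolism or another specified cause are not counted as exacerbations, whether managed in primary care, emergency care or hospital. Record the date, cause and setting of each excluded episode. Repeat the analyses of exacerbation-free survival and of the interval between exacerbations with these episodes counted, and report both. Leave the baseline count under each index's own definition.

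The cost is one sentence in the protocol, a cause field on the 6-monthly follow-up form, and one sensitivity analysis. The downside is that these diagnoses are less often confirmed outside hospital, so some misclassification by care level will remain. Comparing the two analyses shows how much the conclusions depend on it.
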